### Interventions

#### Study visits

Where possible study visits will be matched up with patient’s regular HIV follow-up appointments, either at their usual place of HIV care or the clinical research facility, which is located opposite the HIV unit. Silver Clinic visits are offered both in-person and virtually to ensure ease of access to the service, for PLWH and frailty.

#### Usual care

Participants allocated to the control arm will receive healthcare from their HIV physician, GP and community services as standard (see figure 1). HIV standard of care is provided twice a year and most primary care is provided when actively sought by patients. Participants will be aware of their frailty status, provided with an information leaflet about frailty and will consent to the sharing of the result of their frailty assessment with their GP and HIV physician. Participants will be provided with generic healthy ageing advice but will have no access to the intervention. At the end of 12 months, all control participants, who on assessment continue to require specialist input from ageing experts, will be offered the opportunity to attend the Silver Clinic.

**Figure 1 F1:**
[figure not shown]
Usual HIV care versus the Silver Clinic intervention.

#### The Silver Clinic

Intervention participants will be reviewed within the Silver Clinic based within the Lawson unit, HIV service at RSCH. The intervention consists of a CGA approach delivered in a joint HIV geriatrics clinic, providing multidisciplinary assessment and management of geriatric syndromes affecting OPWH including frailty, falls, polypharmacy, multimorbidity and medication-related problems associated with antiretroviral therapy (see figure 1). It also supports OPWH with social and psychological challenges, by formulating health interventions such as physical activity and peer support. The appointment consists of patient history-taking, physical examination, blood sample and review of medications, cognition, social and mental health. An individualised care plan will then be generated and sent to the patient’s GP/HIV physician. The clinic is delivered once a month with individual appointments of 40 min duration for a total of 16 patients per month. Follow-up appointments within the Silver Clinic will be determined by the Silver Clinic physicians, and therefore, individual to each participant, however, it is not expected that it would be more than two visits for the duration of the trial. Follow-up frequency in the study will include visits at 6 and 12 months.

### Feasibility outcomes and progression criteria

#### Primary outcomes

To determine whether a definitive trial is feasible, we will examine the recruitment rates, completion rates of study outcome measures and retention at specific time points. A priori criteria for trial feasibility and progression to full trial without changes to the trial design are as follows (see table 3 for further details).

Recruitment of 60% of eligible patients.Recruitment of 84 patients within 6 months; from first patient randomised.Retention of 70 participants (allowing up to 15% attrition) to primary end point (6 months).Outcome measure completion for 90% of available participants at each time point.

**Table 3 T3:** Silver study feasibility outcomes, contributing data and progression criteria

Objective	Feasibility outcomes	Contributing data	Progression criteria Green	Amber	Red
1	Identification and recruitment of eligible patients*	Screening and recruitment log	≥60% eligible recruited	59%–40%	<40%
3	Retention of participants at follow-up*	Participation data	≥70 pts at 6 months ≥55 pts at 12 months	74%–60% 59%–40%	<60% <40%
4	Contamination of the control arm	CGA service data	≥10% participants receive a CGA within usual care	≥11%–20%	≥20%
5	Outcome measure completion*	Participation data	Missing data of ≤10% for each measure. Participant-reported acceptability.	11%–25% Some	>25% None
6	Participant satisfaction with care	Participant questionnaires and interviews	Reported as acceptable (or can be with minimal modification)	Reported as acceptable with modification	Intervention not acceptable

*Primary focus; Traffic-light progression criteria^50 51^—Green: likely no concerning issues, Amber: potentially remediable issues, Red: potentially intractable issues.

CGA, comprehensive geriatric assessment.

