### Sample size

This is a feasibility trial, and therefore, not powered to test effectiveness of the intervention compared with standard treatment. However, data will be used to inform the sample size calculation for a future definitive trial. To precisely estimate the SD of the primary outcome for a future trial, a sample size of at least 35 participants per arm is recommended.^42 43^ Based on the local patient numbers (cohort of 2450; 54% over 50 years old), we anticipate recruiting 42 patients per arm, that is, 84 in all allowing for attrition of 15% to be achievable.

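### The retention progression criterion sets green as head-counts and amber and red as percentages, so on the planned 84 participants 63–69 retained at 6 months and 50–54 at 12 months have no colour

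*Protocol article*

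**What the plan says.** The protocol article, under Primary outcomes, introduces its criteria thus: "A priori criteria for trial feasibility and progression to full trial without changes to the trial design are as follows". The retention criterion in that list is "Retention of 70 participants (allowing up to 15% attrition) to primary end point (6 months").

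Table 3 expands this into a traffic-light row for retention, starred as a primary focus. The green cell reads "≥70 pts at 6 months ≥55 pts at 12 months". The amber cell gives 60% to 74% at 6 months and 40% to 59% at 12 months. The red cell gives below 60% and below 40%. No denominator is given for the percentages. The table footnote defines the colours as "Green: likely no concerning issues, Amber: potentially remediable issues, Red: potentially intractable issues" and gives no rule for a result that lies between two bands.

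The Sample size section explains where 70 comes from: "a sample size of at least 35 participants per arm is recommended", and then "we anticipate recruiting 42 patients per arm, that is, 84 in all allowing for attrition of 15% to be achievable".

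**The concern.** A traffic-light rule works only if every possible result has one colour. Here the green floor and the amber ceiling are in different units, and once they are put on the same scale they do not meet. The table's other two starred rows (recruitment and outcome completion) each use a single percentage scale with adjoining bands, so the retention row looks like an oversight. It is not a misread table either, since the running text repeats the count of 70 at 6 months.

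At stake is a pre-specified decision on a primary feasibility outcome. For a result in the gap, someone would have to choose the colour after seeing the data. The two natural repairs give opposite answers for 63–69 at 6 months: amber if the count of 70 is the real cut-off, green if the amber ceiling of 74% is.

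**Working it through.** **Inputs.** Planned total 84, 42 per arm (Sample size). Minimum 35 evaluable per arm (Sample size). Planned attrition 15%, tied to 6 months (Primary outcomes). Bands as printed in Table 3. The denominator of 84 is an assumption; it is the only planned total in the document.

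**The plan's own figure.** 35 / (1 − 0.15) = 41.2, rounded up to 42 per arm, 84 in all. This reproduces exactly. The 70 is 2 × 35.

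**Bands on one scale, N = 84.**

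| | Amber as printed | Amber in counts | Green starts | No colour |
|---|---|---|---|---|
| 6 months | 60%–74% | 51–62 (60.7%–73.8%) | 70/84 = 83.3% | 63–69 (75.0%–82.1%) |
| 12 months | 40%–59% | 34–49 (40.5%–58.3%) | 55/84 = 65.5% | 50–54 (59.5%–64.3%) |

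Both gaps are the same whether percentages are exact or rounded to whole numbers. At 12 months, 50/84 = 59.5% lies above the printed ceiling of 59% and rounds to 60%. It leaves the gap only if 59% is read as anything below 60%.

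**How often a result lands in the gap.** Let X be the number retained, with X ~ Binomial(84, p).

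At 6 months, P(green) = P(X ≥ 70), P(gap) = P(63 ≤ X ≤ 69) and P(amber or red) = P(X ≤ 62):

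| True retention p | Green | Gap | Amber or red |
|---|---|---|---|
| 85% (planned) | 0.727 | 0.267 | 0.005 |
| 80% (assumed) | 0.271 | 0.627 | 0.102 |
| 75% (assumed) | 0.046 | 0.512 | 0.442 |

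At the planned rate the gap takes 0.267 / (1 − 0.727) = 0.98 of all non-green results.

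At 12 months the document plans no retention rate, so all rates are assumed. P(green) = P(X ≥ 55) and P(gap) = P(50 ≤ X ≤ 54):

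| True retention p | Green | Gap |
|---|---|---|
| 60% | 0.181 | 0.401 |
| 65% | 0.514 | 0.364 |
| 70% | 0.847 | 0.138 |
| 75% | 0.981 | 0.018 |

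**Dependence on recruitment.** With a fixed count, the retention needed for green is 70/N. At N = 75 this is 70/75 = 93.3%. At N ≤ 69 it exceeds 100%, so green cannot be reached even with no dropout. The gap widens as N falls: at N = 80 it is 60–69 at 6 months and 48–54 at 12 months. The 6-month gap disappears only when N reaches 94.

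**The case against.** The best defence is that a result of 63–69 plainly misses the criterion for progressing unchanged and is well above red, so amber is the natural ordered reading. The abstract also says that the criteria are used together with the qualitative data, so the decision is not mechanical. This limits the harm: the trial's data and estimates are untouched. It does not settle the colour, because the table sets the amber ceiling at 74% and that figure points just as well to a green floor of 75%.

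A count can also be defended, since 70 serves the precision target for the SD. That is a reason to keep 70 as a requirement of its own, but it does not justify mixing units within one row.

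A reader might infer several stronger points that the document does not support:

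- *That the most plausible results go unclassified.* At the only planned rate, 85%, green is the likeliest 6-month result. The gap becomes the likeliest only at lower rates, such as 75% to 80%, which the document never states.
- *That 15% attrition contradicts 70.* It is true that 84 × 0.85 = 71.4 and that 70/84 means 16.7% attrition. The difference is the slack from rounding 41.2 up to 42 per arm, and it is not an error.
- *That low recruitment turns good retention into a failure.* It blocks green. Red is a percentage, so full retention of 69 participants would not be red.
- *That imbalance between arms would be hidden because the 70 is pooled.* A pooled 70 does not guarantee 35 per arm (42 + 28 = 70), but the Quantitative data section already plans presentation by arm.

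**Conclusion.** The retention row is wrong as written. It mixes counts with percentages, names no denominator, and on 84 participants leaves 63–69 at 6 months and 50–54 at 12 months without a colour. Nothing else in the document resolves this.

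At the planned 85% retention the chance of an unclassified 6-month result is 0.27. It rises to 0.63 if true retention is 80%, so a modest shortfall from plan would most likely receive no pre-specified decision. At 12 months the chance runs from 0.40 down to 0.02 over assumed rates of 60% to 75%.

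These figures assume a denominator of 84 and independent dropout with a common rate. The defect lies in a decision threshold and should be corrected before the retention data are seen.

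**What to change.** Express all three bands as a percentage of those randomised, with no space between them, and state which green cut-off was meant. The document does not show which, so the sponsor must choose.

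- **If the counts are intended.** 6 months: green ≥83.3% (70/84), amber 60% to <83.3%, red <60%. 12 months: green ≥65.5% (55/84), amber 40% to <65.5%, red <40%.
- **If the amber ceilings are intended.** 6 months: green ≥75%, amber 60% to <75%, red <60%. 12 months: green ≥60%, amber 40% to <60%, red <40%. The 70 in the running text is then changed to match.

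A percentage alone drops the precision floor: 50 retained of 60 is also 83.3%, with only about 25 per arm. If 70 evaluable participants (35 per arm) are still needed to estimate the SD, keep that as a separate criterion.

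The cost is one reworded table row and, on the second choice, one reworded sentence. A separate precision criterion would add one line. No new data are needed.

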## Methods and analysis

### Trial design

The Silver Clinic feasibility study will use a mixed-method RCT design. Participants will be randomised 1:1 to two parallel groups: usual care or the Silver Clinic intervention, (including the CGA). Quantitative data (including process data and participant outcome measures at baseline, week 26 and week 52) will be collected alongside nested qualitative interview data from a subset of participants.

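### Table 3's retention row gives Green as head counts and Amber/Red as percentages that do not meet, so with 84 randomised 63–69 retained at 6 months and 51–54 at 12 months have no colour

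*Protocol article*

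**What the plan says.** The section on feasibility outcomes and progression criteria lists retention among the primary outcomes, and Table 3 stars it as a primary focus. The Green cell reads "≥70 pts at 6 months ≥55 pts at 12 months". The Amber cell gives 74% down to 60% for 6 months and 59% down to 40% for 12 months. The Red cell gives below 60% and below 40%. No denominator is named for the percentages.

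The text criterion above the table repeats the 6-month count: "Retention of 70 participants (allowing up to 15% attrition) to primary end point (6 months". The footnote defines three colours only: "Green: likely no concerning issues, Amber: potentially remediable issues, Red: potentially intractable issues". Nothing assigns a colour to a result lying between two bands.

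The planned size comes from the Sample size section: "a sample size of at least 35 participants per arm is recommended", and then "we anticipate recruiting 42 patients per arm, that is, 84 in all allowing for attrition of 15% to be achievable".

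**The concern.** A traffic-light rule fixed in advance should give every possible result exactly one colour. This row mixes units, and once the counts are put on the percentage scale a range between Green and Amber is left empty. Elsewhere in Table 3 the percentage bands are adjacent to the whole percent: recruitment is at least 60, 59–40, below 40; missing data is at most 10, 11–25, above 25. By that pattern Amber tops of 74% and 59% imply Green from 75% and 60%, which is not what the Green cell says. So the row carries two different Green limits.

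Two things are at stake. A result in the gap would have to be coloured after the data are seen, which criteria set in advance are meant to avoid. And because Green is a fixed count, the percentage it demands changes with the number recruited, so the row does not measure retention alone.

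**Working it through.** **Inputs.** Planned total 84, 42 per arm (Sample size); 35 per arm needed for the SD (Sample size); 15% attrition (Sample size and the text criterion); Table 3 limits as above. Assumption: the percentages are of the 84 randomised, since no denominator is stated.

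**The plan's own figure.** 35 / (1 − 0.15) = 41.2, rounded up to 42 per arm; 2 × 42 = 84. This reproduces. The Green count of 70 is 2 × 35. As a share of 84 it allows 1 − 70/84 = 16.7% attrition rather than 15%; that is the effect of rounding up to 42 and not a separate error.

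**Bands at 84 randomised.**

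| | Red | Amber | No colour | Green |
|---|---|---|---|---|
| 6 months | 0–50 | 51–62 | 63–69 | 70–84 |
| 12 months | 0–33 | 34–49 or 50 | 50 or 51–54 | 55–84 |

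- 6 months: 62/84 = 73.8%, the last Amber count; 63/84 = 75.0%; 69/84 = 82.1%; 70/84 = 83.3%. The gap of 63–69 is the same whether percentages are exact, rounded or truncated.
- 12 months: 49/84 = 58.3%; 50/84 = 59.5%; 51/84 = 60.7%; 54/84 = 64.3%; 55/84 = 65.5%. The count of 50 is Amber only if 59.5% is truncated to 59%; if exact or rounded it also has no colour. The gap common to all readings is 51–54.

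**Green implied by the Amber tops.** 0.75 × 84 = 63 and 0.60 × 84 = 50.4, so at least 63 and at least 51, against the printed 70 and 55. Counts and percentages would meet only near 70/0.75 = 93.3 or 55/0.60 = 91.7 recruited, and the article contains no such number.

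**Chance of no colour.** X is the number retained, binomial with n = 84 and true retention p.

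| 6 months, p | P(X ≥ 70), Green | P(63 ≤ X ≤ 69), no colour |
|---|---|---|
| 85% | 73% | 27% |
| 80% | 27% | 63% |
| 75% | 5% | 51% |

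At 12 months the article gives no planning value, so a range is shown. P(51 ≤ X ≤ 54) is 31% at p = 60%, 30% at 65.5%, 13% at 70% and 2% at 75%.

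**Dependence on recruitment.** 70/80 = 87.5%; 70/75 = 93.3%; 70/70 = 100%. With 69 recruited and all 69 retained, the 6-month result is not Green (69 < 70), not Amber (100% > 74%) and not Red. At true retention of 85%, P(Green at 6 months) falls from 73% with 84 recruited to 33% with 80 and 2% with 75.

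**The case against.** The best defence is that the gap has one sensible reading. The text criteria govern progression without design changes, and there the 6-month limit is 70, so 63–69 is not Green. Red starts only below 60%, so it is not Red either. That leaves Amber. The abstract adds that the criteria are used together with the qualitative data, so no single colour decides. This stands, and it limits the severity: a reader might infer that the gap sets go against stop, and the document does not support that.

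Two other stronger readings also fail. One is that the gap is where the result is most likely to fall. At the plan's 15% attrition with all 84 recruited, Green is likelier (73% against 27%); the gap becomes the likeliest result at true retention of 80% or 75%, or if recruitment falls short. The other is that any recruitment shortfall fails the retention criterion. With 80 recruited, 70 retained is still Green. Green is impossible at 6 months only below 70 recruited and at 12 months only below 55.

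A further defence is that the count is deliberate, since 70 retained delivers the 35 per arm needed for the SD. That is fair, and the target should be kept. It does not explain why the neighbouring bands are in other units and do not reach it.

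The gap is not a table-extraction fault, since the text repeats the 70. Nor is it detail left to another document, because the limits are printed and conflict.

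**Conclusion.** The retention row is wrong as written and should be fixed. At 84 randomised it leaves seven possible results at 6 months (63–69) and four or five at 12 months (51–54, and 50 unless percentages are truncated) without a colour. Its Amber tops imply Green limits of 63 and 51, in conflict with the printed 70 and 55. The chance of an uncoloured 6-month result runs from 27% to 63% over true retention of 75% to 85%; at 12 months it runs from 2% to 31% over 60% to 75%.

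These figures assume that participants randomised are the denominator, that all 84 are recruited, and that participants drop out independently with a common probability. The existence of the gap needs only the first two.

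The consequence is a labelling choice between Green and Amber made after the data are seen, plus a retention criterion that partly measures recruitment. It is not an ambiguity between proceeding and stopping.

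**What to change.** Before the 6-month data are reviewed, restate the row as one contiguous set of bands with participants randomised as the stated denominator. Because the text criterion repeats 70 at 6 months, the natural repair keeps the Green counts and extends Amber up to them. At 84 randomised:

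| | Green | Amber | Red |
|---|---|---|---|
| 6 months | ≥70 (83.3%) | 51–69 (60% to below 83.3%) | ≤50 (below 60%) |
| 12 months | ≥55 (65.5%) | 34–54 (40% to below 65.5%) | ≤33 (below 40%) |

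This is a choice: it gives up the printed Amber tops of 74% and 59%. If the sponsor meant Green from 75% and 60%, then the 70 and 55 must change instead, and the text criterion with them.

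Report the absolute target of 70 retained (35 per arm for the SD) as a separate item. A recruitment shortfall is then not read as poor retention, and the precision target is not lost: with 75 randomised, 63 retained is 84.0%, which is good retention but short of 70.

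The article gives no rule for combining the two time points, and none is proposed here. The cost is the wording of one table row and one added reporting line; no extra data or participants are needed.

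### In Table 3 the green inequality for control-arm contamination is reversed, so the row contradicts itself and cannot be scored as printed

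*Protocol article*

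**What the plan says.** The Table 3 row numbered 4 is titled "Contamination of the control arm" and draws on CGA service data. Its green cell reads "≥10% participants receive a CGA within usual care". Amber runs from 11% to 20%, with a ≥ sign before the 11%, and red is 20% or more. The footnote gives the colours their meaning: "Green: likely no concerning issues, Amber: potentially remediable issues, Red: potentially intractable issues".

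Three other statements bear on the direction of the row:

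- The Usual care section says of controls: "Participants will be provided with generic healthy ageing advice but will have no access to the intervention".
- The Silver Clinic section describes the intervention as a CGA approach.
- The row of Table 3 on outcome measure completion, where a lower percentage is also better, has green as "Missing data of ≤10% for each measure", followed by 11%–25% for amber and above 25% for red.

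The contamination threshold is not restated or corrected anywhere else in the article.

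**The concern.** A CGA given to a control participant narrows the contrast between the arms, so a low percentage is the good result. The green cell asks for a high one. Read literally, green has no upper limit and covers everything in amber and red, while results below 10%, which the trial hopes for, have no colour.

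Progression criteria are fixed in advance so that the reading of the results does not depend on what they turn out to be. Here the direction of one criterion has to be inferred. If that is left until the contamination rate is known, the reading of the row is open to challenge whichever way it goes. Contamination is also a practical possibility: controls attend the same HIV service that houses the Silver Clinic, and their frailty result is shared with their GP and HIV physician.

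**Working it through.** **Inputs**

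- Bands as printed in Table 3, with p the percentage of controls receiving a CGA: green p ≥ 10; amber 11 ≤ p ≤ 20; red p ≥ 20.
- Allocation (Trial design): "Participants will be randomised 1:1 to two parallel groups".
- Minimum per arm (Sample size): "a sample size of at least 35 participants per arm is recommended".
- Planned arm size (Sample size): "we anticipate recruiting 42 patients per arm, that is, 84 in all allowing for attrition of 15% to be achievable".

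**Step 1: reproduce the arm size.** 35 / (1 − 0.15) = 41.2, rounded up to 42 per arm and 84 in all. This agrees with the plan. The contamination cut-offs are stated without a derivation, so there is nothing further to reproduce.

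**Step 2: apply the printed bands to every possible count k, with p = 100 × k / 42.** The boundary values are 4/42 = 9.5%, 5/42 = 11.9%, 8/42 = 19.0% and 9/42 = 21.4%.

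| Contaminated controls (of 42) | Percentage | Bands met as printed |
|---|---|---|
| 0–4 | 0–9.5% | none |
| 5–8 | 11.9–19.0% | green and amber |
| 9–42 | 21.4–100% | green and red |

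Of the 43 possible counts, 5 meet no band and 38 meet two. None meets exactly one.

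**Step 3: repeat with 35 controls**, the minimum the plan aims to keep per arm. Counts 0–3 (0–8.6%) meet no band. Counts 4–6 (11.4–17.1%) meet green and amber. Count 7 (7/35 = 20.0%) meets all three. Counts 8–35 (22.9–100%) meet green and red.

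**Step 4: change only the green sign to ≤.** With 42 controls every count then falls in exactly one band: 0–4 green, 5–8 amber, 9 or more red. Two loose ends remain. Exactly 20% is still both amber and red, which matters for 7 of 35 but for no count out of 42. Values above 10% and below 11% have no band, although no count out of 42 or 35 lands there.

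**Step 5: which direction is intended?** Amber and red rise with contamination, the footnote puts green at the favourable end, and the missing-data row has the same layout with ≤10% for green. All three require ≤10% here.

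**The case against.** The best defence is that this is a slip of one sign whose correction is evident from the table itself, in a row of secondary standing. Much of that stands. Only the green cell is reversed; amber and red run the right way. The intended threshold can be recovered from the document, and the article says a full statistical analysis plan will be agreed before database lock, so the correction can still be made before the final analysis. Sample size, randomisation, data collection and effect estimates are untouched.

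A reader might infer that the row would wave through a trial whose arms are not separated, or would stop one with no contamination. The documents support neither. Nine or more contaminated controls out of 42 meet red as well as green, so the row gives conflicting signals and not a clean pass. Contamination has no asterisk for primary focus, and it is not among the four listed criteria (share of eligible patients recruited, 84 recruited within 6 months, retention, outcome completion). A trial with no contaminated controls can meet all four, and nothing says that one Table 3 row settles progression alone.

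The defence does not remove the error. The row stands under the progression criteria, and the protocol states its threshold wrongly; this is not detail left to a later document. A fault in reading the PDF is an unlikely explanation, because the ≤ sign in the missing-data row of the same table came through intact.

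**Conclusion.** Wrong as written. The green inequality in the contamination row is reversed, and the row as printed gives no single colour to any count out of 42 (or out of 35). A second, smaller fault is the overlap of amber and red at exactly 20%.

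The consequence is confined to this row of the progression assessment. The counts assume that the denominator is the control arm, as the row title indicates, and that it holds the planned 42; the check at 35 shows the same pattern. The reversal itself does not depend on the denominator.

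**What to change.** Before the progression decision, reword the row with its denominator named and with bands that neither overlap nor leave gaps:

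- Green: ≤10% of control-arm participants receive a CGA within usual care (0–4 of 42).
- Amber: >10% to 20% (5–8 of 42).
- Red: >20% (9 or more of 42).

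This keeps the plan's own cut-offs of 10% and 20%. It closes the gap between 10% and 11% and assigns exactly 20% to amber; with 35 controls, 0–3 would be green, 4–7 amber and 8 or more red. The cost is a one-line correction to Table 3 and to the matching text of the full protocol, carried into the statistical analysis plan. No extra data are needed and participants are not affected.
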